### Usual care

At the time of designing this study, lung screening was not included in the list of health recommendations like other preventive services (e.g., breast cancer screening, colorectal cancer screening) in the EHR to prompt providers. Providers had to utilize the smoking history data included in the record to identify patients eligible for lung screening. However, the total pack-years field in the EHR had a large amount of missingness (90% on average are missing pack-years) across the 4 practice sites, possibly due to the field lacking automation. Usual care in MedStar primary care is expected to change as a result of ongoing related work led by our team. New forms are being released to improve the assessment of tobacco use, including automated calculation of pack-years, and to facilitate smoking cessation and lung screening referrals by displaying in the recommendations tab for eligible patients.

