### Measures

We will use mixed-methods and multilevel assessments (Table 1). At the *patient-level*, participants will be assessed at baseline and 1-week post-visit to measure the primary outcomes: provider-patient discussion (“Did you have a discussion with your doctor about lung screening?”), screening intentions (“Do you plan to have a CT scan to check for lung cancer in the next 6 months?”), and knowledge using 11 true/false items from the literature [47]. We will administer the Questionnaire on the Quality of Physician–Patient Interaction scale to measure patient-reported provider-patient communication [48]. The Lung Screening Health Beliefs Scale will measure perceived risk, self-efficacy, benefits, and barriers [49]. The Consumer Health Activation Index will be administered to measure patient activation [35]. We will evaluate potential moderators including race (non-Hispanic African American vs. non-Hispanic White vs. other), smoking status (current vs. former), and health literacy (“How often do you find numbers, figures, or graphs to be useful in making a health-related decision?”) [50].

**Table 1 Tab1:** Complete measures

		**T0**	**T1**	**T2**
		**Baseline**	**1 week**	**6 months**
***Patient-level variables***	*Primary outcomes*: Provider-patient discussion, lung screening intentions, screening knowledge	**X**	**X**	
	*Secondary outcomes*: Lung screening referrals, completion rates (EHR)	**X**		**X**
	*Moderators*: Race, smoking status, health literacy	**X**		
	*Intervention targets*: Physician–patient communication, perceived risk, self-efficacy, benefits/barriers, patient activation, attended visit/visit type	**X**	**X**	
	*Covariates*: Demographics, social determinants of health, tobacco behaviors, cancer screening history, psychological variables (e.g., stigma, medical mistrust)	**X**		
***Provider-level variables***	Demographics	**X**		
	Lung screening practices	**X**		**X**
	Lung screening attitudes	**X**		**X**
	Intervention acceptability, usability, intervention, effectiveness			**X**
***Implementation variables***	Reach: % of patients offered trial enrollment and the % enrolled out of the number of eligible patients who had a visit during the recruitment period	**Pre-post implementation**		
	Effectiveness: screening referrals and screening completion rates			
	Adoption: % of messages opened by the receiving provider; fidelity of the patient component			
	Implementation: feasibility, acceptability			

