At the *provider-level*, we will assess provider demographics (age, race and ethnicity, years in practice, academic appointment), checklist of the current lung screening process, and attitudes toward lung screening using semi-structured interviews pre-post trial. We will use items from the validated Technology Acceptance Model to measure the usability and effectiveness of a technology-oriented strategy [51].

Secondary outcomes, screening referrals, and screening completion rates will be extracted from the EHR database at 6-month post clinic enrollment. To measure temporal trends at the *clinic-level,* lung screening orders and completion rates will also be collected 12-month pre- and post-study. Additionally, in pre-implementation, we conducted semi-structured interviews with the Medical Directors and Operations Managers for contextual purposes. We asked questions about current practice volume, standard rooming practice, workflow for reviewing and addressing health recommendations for lung cancer screening and other preventive services, and information on screening referrals and follow-up.

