### Sample size and power

All power calculations were performed for the primary outcomes (provider-patient discussion, screening intentions, and knowledge), using intention-to-treat principles, and a significance level of 0.05. We will have 83% power to detect a difference of 12% for the provider-patient screening discussion, a difference of 15% for likely screening intention, and an effect size of 0.33 for the screening knowledge score. For the moderation analyses, we will have > 80% power to detect an effect size of 0.50 with equal subgroups (e.g., Black vs White, high vs. low literacy levels).

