### Statistical analysis plan

We will examine the distributions of all variables to describe the characteristics of the study population. We will conduct analyses using *t*-tests, *χ*^2^ tests, and Pearson or Spearman correlation coefficients to assess the bivariate associations between the baseline characteristics and the outcome variables. Bivariate analyses will also be conducted to assess the associations between the study arm and baseline characteristics. Owing to any significant differences detected at the 0.05 level, the variables associated with both the study arm and the outcome of interest will be entered as covariates in subsequent analyses. To test the overall difference between the study arms on the primary outcomes, we will conduct logistic regression models (for provider-patient discussion — yes/no, screening intentions — likely/unlikely) and a linear regression model (for the screening knowledge score). Logistic regression analyses will also be conducted on the secondary screening outcomes (lung screening referral — yes/no, lung screening completion — yes/no). This study will explore potential moderators (e.g., race, health literacy, smoking status). That will be done by evaluating the presence of interactions between the moderators and study arm, one at a time, after adding them to the regression models described above. In sensitivity analyses, we will evaluate the robustness of our findings by using versions of the above models with generalized estimating equations (GEE). These models will use the sites as clusters, and assume an exchangeable working correlation structure.

For the qualitative analysis, we will use a deductive thematic analysis based on a priori PRISM constructs, with additional codes added as needed. Initial codes will be generated by two coders and each of the coders will review two transcripts for each sub-population (i.e., patient and provider) to reach a consensus on the coding framework and application of codes prior to splitting up the remaining transcripts.

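### The baseline value of each primary outcome is collected but not fixed as a covariate; its entry depends on a 0.05 significance screen

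*Protocol article*

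**What the plan says.** The Measures section states that "participants will be assessed at baseline and 1-week post-visit to measure the primary outcomes", and Table 1 marks discussion, intention and knowledge at both T0 and T1.

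The Statistical analysis plan section specifies logistic regression for discussion and intention and "a linear regression model (for the screening knowledge score") for knowledge. No T0 outcome value is named in any of these models. Covariates are chosen by testing: baseline characteristics are examined against arm and against outcome, and only those significant at 0.05 on both are carried forward. The GEE sensitivity analyses are versions of the same models with sites as clusters, so they inherit the same rule.

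The four clinics are not randomised. The Clinical setting section matches them on having a CT scanner on site and on minority representation. For the secondary outcomes, Measures adds that "lung screening orders and completion rates will also be collected 12-month pre- and post-study", for the purpose of describing clinic-level trends over time.

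**The concern.** Without randomisation, nothing in the design balances prior knowledge, intention or earlier discussion between the two sets of clinics. The T0 value of an outcome is the most direct measured confounder of its T1 value and usually its strongest predictor.

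A significance screen is a poor gatekeeper for such a variable. Whether a gap reaches p < 0.05 depends on sample size as well as on the gap, so a moderate imbalance can pass untouched into the estimate. Where the arms happen to be balanced, the screen drops the covariate, and the precision it would have given is lost. Two things are at stake: some residual bias, and power for knowledge that the planned data could supply at no extra collection cost.

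**Working it through.** **Inputs.** From Sample size and power: "a significance level of 0.05" (two-sided assumed, since sidedness is not stated), power of 83%, and a knowledge effect of 0.33 SD. From Patient recruitment and procedures: 184 per arm. The T0–T1 correlation r is not given, so a range is used. Patients are treated as independent throughout.

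**Step 1. Reproduce the stated power.** For knowledge, power = Φ(0.33 × √(n/2) − 1.96).
- n = 184: 0.33 × 9.592 − 1.96 = 1.205, giving 88.6%.
- n = 156: 0.33 × 8.832 − 1.96 = 0.954, giving 83.0%.

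Since 156 / (1 − 0.15) ≈ 184, the stated 83% reproduces if 15% loss is assumed; the article does not state a loss. The binary outcomes are compatible with the same n (normal approximation, pooled variance under the null):
- "a difference of 12% for the provider-patient screening discussion": 82.7% for 10% against 22%.
- "a difference of 15% for likely screening intention": 84.6% at a control rate of 20%, 81.1% at 25%.

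The control rates are assumptions. The stated power thus matches an unadjusted two-sample comparison with no baseline covariate.

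**Step 2. Knowledge power with T0 always in the model.** The residual SD falls to √(1 − r²), so power = Φ(0.33 / √(1 − r²) × √(156/2) − 1.96).

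| r | √(1 − r²) | Power |
|---|---|---|
| 0 (unadjusted) | 1.000 | 83.0% |
| 0.3 | 0.954 | 86.3% |
| 0.5 | 0.866 | 92.0% |
| 0.6 | 0.800 | 95.4% |

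**Step 3. The gap that the screen lets through.** An observed standardised baseline difference is non-significant up to 1.96 × √(2/n). That is 0.22 SD at n = 156 and 0.20 SD at n = 184.

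**Step 4. Simulate the stated rule.** Settings: 5,000 runs each, 156 per arm, r = 0.5, normal data, T0 knowledge as the only candidate covariate. T0 enters when it is significant at 0.05 against both arm and outcome. With no true effect:

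| True baseline gap (SD) | T0 enters | Mean bias: stated rule | Mean bias: T0 never used | Mean bias: T0 always used | Rejection rate: stated rule |
|---|---|---|---|---|---|
| 0.10 | 14% | 0.031 | 0.050 | about 0 | 5.1% |
| 0.15 | 26% | 0.039 | 0.076 | about 0 | 5.0% |
| 0.20 | 42% | 0.034 | 0.098 | about 0 | 5.5% |
| 0.30 | 76% | 0.019 | 0.151 | about 0 | 5.4% |

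With no baseline gap and a true effect of 0.33 SD, simulated power is 82.1% if T0 is never used, 83.0% under the stated rule and 91.1% with T0 always used. The rule recovers 83.0 − 82.1 = 0.9 of the 91.1 − 82.1 = 9.0 points available.

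**The case against.** The strongest reply is that the plan does adjust. The screen can admit a T0 outcome, and it does so most often when the imbalance is large. A reader might infer that the arm comparisons ignore the T0 data altogether. The article does not support that: it never says that T0 outcome values are excluded from the baseline characteristics being screened.

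A reader might likewise take the bias to be 0.2 × 0.5 = 0.10 SD for a 0.2 SD gap, about 30% of the 0.33 SD target. That applies only if T0 never enters. Under the stated rule the average is 0.034 SD, about 10% of the target, and the rejection rate in these settings stays near 5%. This part of the reply stands and limits the bias argument to a small effect.

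A second reply is that the stated power is met without covariates, so extra precision is an improvement and not the correction of an error. That is also fair. But the covariate rule is written into the article and not left to an unseen document, and it gives up information already collected.

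Three further inferences go beyond the documents.
- **A required difference-in-differences analysis.** The article says "Usual care in MedStar primary care is expected to change as a result of ongoing related work led by our team", which may suggest that only a pre/post contrast could isolate the strategies. The comparison clinics already address changes common to both arms; only uneven uptake would confound. The clinic-level data already have a stated trend purpose, cover orders and completion only, and come from four clinics. A full analysis would need visit denominators and form-release dates that the article does not list.
- **T0 adjustment as a cure for the discussion item.** The item as quoted names no visit, so an earlier discussion could be reported at T1. Adding T0 to the model would not by itself stop that, and any lead-in to the questionnaire is not shown.
- **Equal gains for every outcome.** The benefit is clearest for knowledge. A T0 discussion cannot concern the index visit, and in logistic models adjustment changes the odds ratio to a conditional one.

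The Discussion section also concedes that the quasi-experimental design limits causal conclusions. That is correct, but it does not replace using a measured confounder.

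**Conclusion.** The point holds in a limited form: adjustment for the T0 value of each primary outcome is left to a significance test when it should be fixed in advance. The residual bias is small, about 0.03 to 0.04 SD on average for true knowledge gaps of 0.10 to 0.20 SD at r = 0.5. The precision loss for knowledge is the larger matter: when the arms are balanced at baseline, about nine tenths of the available gain is forgone at r = 0.5.

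The sizes rest on an assumed r, an assumed 15% loss, two-sided testing and independent patients. At r = 0.3 the gain is only about 3 points of power (83.0% to 86.3%). Because clustering by clinic is ignored, the figures show the relative value of T0 adjustment, not the power the study will actually have. T0 adjustment leaves unmeasured clinic differences and clustering untouched.

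**What to change.** State in the Statistical analysis plan that each primary model (knowledge, intention, discussion) includes the T0 value of the same outcome as a mandatory covariate, regardless of the 0.05 screen, and that the GEE versions do the same. State also that the odds ratios for intention and discussion are conditional on T0. The cost is a change of wording and one degree of freedom per model; Table 1 already schedules the data.

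Two optional additions:
- Tie the T1 discussion item to the index visit, to match the Discussion section's description of the endpoint as discussion at that visit.
- Report the 12-month pre- and post-study clinic order and completion rates by arm, as a descriptive supporting contrast for the secondary outcomes only.

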There are several drivers of lung cancer health disparities, including forms of oppression that span across the cancer continuum and occur at multiple levels (e.g., individual, societal) [11]. This includes differences in exposure to risk factors (e.g., greater exposure to air pollution and tobacco smoke), lack of insurance and barriers to healthcare access, historical medical racism and medical mistrust, discrimination within the healthcare system including differential discussion based on a patient’s race, and underrepresentation in clinical trials that inform the development of screening guidelines and novel therapies. It is also well documented that the tobacco industry has used long-standing predatory practices to target minoritized groups resulting in greater tobacco exposure and tobacco-related disparities, including lung cancer [12].

Lung cancer screening may be particularly beneficial for African Americans because they are more likely to have advanced disease and lower survival compared to Whites [13]. Additionally, data from the NLST suggested that lung cancer screening reduces lung cancer mortality to a greater extent in African Americans compared to all racial groups (hazard ratio, 0.61 vs. 0.86) [14]. However, lung cancer screening rates are consistently low across all racial and ethnic groups [6], and data suggest rates of uptake are lower among African Americans compared to Whites [15–17]. In the context of lung cancer screening, there are several factors that may contribute to racial disparities including (1) current screening guidelines do not take into account additional risk factors and differences in smoking patterns among individuals who may benefit from early detection, (2) socially disadvantaged areas that contribute to a higher smoking rate and higher lung cancer incidence, but have fewer accredited screening facilities creating an access issue, and (3) medical mistrust and the smoking-related stigma that can stand in the way of seeking screening or other forms of medical care [18]. Evidence points to the need for multilevel methods that simultaneously address multiple determinants to increase screening rates and decrease lung cancer morbidity and mortality in minoritized populations [19–21].

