## Methods/design

### Study aims

This study will target provider- and patient-level barriers in order to improve utilization of lung screening and to achieve equity in screening rates by conducting a quasi-experimental study comparing a Multilevel Intervention to Usual Care. The Multilevel Intervention will perform inreach to educate patients about screening prior to their visit. At the same time, an EHR communication tool, similar to email, will send a reminder to primary care providers prior to scheduled visits with screening-eligible patients.

The *specific aims* of the trial are to (1) test the impact of the multilevel strategies on primary outcomes (provider-patient discussion, screening intentions, and knowledge) and secondary outcomes (screening referrals and screening completion rates) and (2) evaluate the implementation outcomes (adoption, feasibility, acceptability, fidelity).

The *hypotheses* are (1) participants in the Multilevel Clinics who receive the provider- and patient-level strategies will be significantly more likely to report having a screening discussion, intending to be screened, and having greater knowledge compared to the Comparison Clinic participants; (2) the multilevel, bundled strategies will increase screening referrals made by providers in the Multilevel Clinics; and (3) completion rates among the participants will be higher among the Multilevel Clinic participants compared to the Comparison Clinic participants. Finally, we will explore whether Health Disparities Framework factors (e.g., race, education, health literacy) moderate the outcomes (e.g., we expect that African Americans will have significantly greater knowledge in the Multilevel Clinics vs. the Comparison Clinics, whereas the strategies will have less of an impact among Whites).

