## Discussion

Guided by the Health Disparities Research and PRISM frameworks that take into account the multilevel determinants of cancer screening disparities and the multilevel interactions needed to understand and address these disparities, this quasi-experimental study will test the effect of provider- and patient-level implementation strategies to improve patient-provider discussion about lung screening and increase equity in lung screening rates between African American and White primary care patients. Through mixed-methods and multilevel assessments, this study is well-positioned to evaluate the impact of a provider prompt as well as a patient inreach and education component on the adoption of lung screening as an evidence-based intervention.

The planned study has three innovative aspects. First, this study will be one of the first to test the impact of multilevel implementation strategies on lung screening discussions and screening rates. We will test provider prompts that will serve as a reminder to discuss screening, and simultaneously target the patient level to address knowledge, communication, and psychological barriers to screening. It is well established that there are multiple levels of influence involved in lung screening; however, few studies have intervened beyond the individual level [24–27]. Second, the proposed study is applying the Health Disparities Research Framework to target two levels of influence, the patient-level and provider-level, that contribute to disparities in screening outcomes. This study is grounded in the disparities framework and these factors will be examined in moderation analyses. Finally, this study is testing the impact of implementation strategies aimed at the equitable adoption of lung cancer screening in diverse primary care practice settings. This study will examine the effect of these strategies on guideline-concordant provider-patient screening discussion and behaviors. The proposed strategies have the potential to increase adoption of this evidence-based intervention, improve outcomes, and mitigate racial disparities between African American and White patients who are eligible for lung screening.

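### For the binary outcomes, race moderation is assessed only as a ratio of odds ratios, which does not by itself show whether the racial gap in screening rates has changed

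*Protocol article*

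**What the plan says.** The Study aims section of the protocol article says the trial is meant "to achieve equity in screening rates". The Discussion repeats the target as a wish to "increase equity in lung screening rates between African American and White primary care patients". The Background reports that "data suggest rates of uptake are lower among African Americans compared to Whites", but gives no size for the difference.

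The analysis of moderators, race among them, is fixed in the Statistical analysis plan section: "evaluating the presence of interactions between the moderators and study arm, one at a time, after adding them to the regression models described above". The models meant there are logistic for provider-patient discussion and screening intentions. For referral and completion, "Logistic regression analyses will also be conducted on the secondary screening outcomes". Only knowledge differs, with "a linear regression model (for the screening knowledge score"). The status of the moderation work is exploratory: "This study will explore potential moderators (e.g., race, health literacy, smoking status").

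The article states no race-specific rate, risk difference by race, or change in the racial gap as a quantity to be estimated.

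**The concern.** Referral and completion are the outcomes that carry the aim of equity in screening rates. For them the only stated race analysis is an arm-by-race product term in a logistic model. That term asks whether the odds ratio for the intervention is the same in African American and White patients. A reader interested in equity will usually also ask whether the difference in rates between the two groups became smaller. When the starting rates differ, these are different questions and can have different answers.

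At stake is the interpretation. A null interaction could be read as no effect on the disparity although the absolute gap had widened. An interaction odds ratio favouring African American patients could be read as progress although the gap in percentage points had not moved. The Discussion presents this study as preliminary data for a later cluster randomized trial of equitable screening, so such a reading would carry forward. The protocol's own Sample size and power section expresses the effects on the binary primary outcomes as absolute differences (12% and 15%), so the odds scale is not the only one the plan uses.

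**Working it through.** **The plan's own figure.** There is none for the racial gap. The only moderation figure is over 80% power for an effect size of 0.50 with equal subgroups (368/4 = 92 per arm-by-race cell).

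- Read as an arm contrast within one subgroup, the standard error is √(2/92) = 0.147, and power is 92.4%.
- Read as the interaction contrast, it is √(4/92) = 0.209, and power is 66.9%.

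The definition of the effect size is not given, so the figure cannot be settled. It says nothing about rates in either reading.

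**Inputs.** The Background gives overall uptake between 3% and 20% and says uptake is lower in African American patients. It gives no race-specific rates, so all race-specific rates and odds ratios below are assumptions, shown over a range. The last row lies outside the 3–20% range and stands for an outcome with high rates.

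**Step 1: interaction odds ratio exactly 1.** Apply one common odds ratio (OR) to both groups: p′ = OR·p / (1 − p + OR·p). For example, at OR 3, 5% becomes 0.15/1.10 = 13.6% and 10% becomes 0.30/1.20 = 25.0%.

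| Usual care, White / African American | OR | Multilevel, White / African American | Gap, points | Rate ratio |
|---|---|---|---|---|
| 6.5% / 3% | 3 | 17.3% / 8.5% | 3.5 → 8.8 | 2.17 → 2.03 |
| 10% / 5% | 2 | 18.2% / 9.5% | 5.0 → 8.7 | 2.00 → 1.91 |
| 10% / 5% | 3 | 25.0% / 13.6% | 5.0 → 11.4 | 2.00 → 1.83 |
| 15% / 10% | 3 | 34.6% / 25.0% | 5.0 → 9.6 | 1.50 → 1.38 |
| 20% / 10% | 3 | 42.9% / 25.0% | 10.0 → 17.9 | 2.00 → 1.71 |
| 50% / 40% | 3 | 75.0% / 66.7% | 10.0 → 8.3 | 1.25 → 1.125 |

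The logistic interaction is null in every row. Over a grid of rates from 3% to 20% and odds ratios from 1.5 to 5, the absolute gap widened in every scenario and more than doubled in 37% of them.

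**Step 2: the reverse case.** Let both groups gain 10 points, so the gap stays at 5.

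- 5% to 15%: OR = (0.15/0.85)/(0.05/0.95) = 3.35.
- 10% to 20%: OR = (0.20/0.80)/(0.10/0.90) = 2.25.
- Interaction odds ratio = 3.35/2.25 = 1.49, in favour of African American patients, with no change in the gap.

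**Step 3: precision of the alternative estimate.** The difference in risk differences has standard error √[Σ p(1 − p)/92] over the four cells. For 10%/5% and OR 3: (0.0900 + 0.0475 + 0.1875 + 0.1178)/92 = 0.00481, with square root 0.0694, so the 95% half-width is 1.96 × 0.0694 = 13.6 points. Across the four usual-care pairs from 6.5%/3% to 20%/10% at OR 3 it is 11.4 to 16.9 points, and power to detect the change is 8% to 15%. This ignores clustering in four clinics and assumes equal race groups.

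**The case against.** The strongest reply has four parts.

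- **Scale.** The protocol never defines equity as an absolute gap. In the 10%/5% example the rate ratio falls from 2.00 to 1.83 while the difference grows, so neither scale is the only correct one. This stands. A reader might infer that the plan gives a wrong answer to the equity question, but the documents do not support that. They support only that the stated test does not answer the question on the scale of rates.
- **Reach and size.** A reader might infer that all race moderation is on the odds scale, or that the gap would more than double unnoticed. Knowledge, a primary outcome and the only one with a stated directional expectation by race, has a linear model. Doubling needs low rates and a large common odds ratio: at least 2.25 at 6.5%/3%, 2.46 at 10%/5% and 3.33 at 15%/10%. At 20%/10% the gap never exceeds twice its starting value.
- **Premise.** The Background statement concerns general uptake. This cohort is currently non-adherent and has a scheduled visit, and its usual-care rates by race are unknown. This also stands, which is why the result is conditional.
- **Status and power.** Moderation is exploratory, and a fuller analysis plan may add risk differences. At 92 per cell, an interaction odds ratio of 1.49 has a log standard error of about 0.71 and power of about 9%, so the plan would rarely declare it. The proposed contrast is no better powered.

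The last point limits the consequence but does not remove the mismatch. The article does more than stay silent: it names the method for the moderator question, and for the binary outcomes that method measures something other than rates. Low power is also a reason to look at estimates with intervals and not at whether an interaction is present.

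**Conclusion.** The point holds in a limited form. For the four binary outcomes, most importantly referral and completion, the stated race analysis is a ratio of odds ratios, while the stated aim concerns rates. If usual-care rates differ by race, a null interaction is compatible with a materially different absolute gap. Across the assumed usual-care pairs from 6.5%/3% to 20%/10%, a common odds ratio of 3 multiplies the gap by about 1.8 to 2.5, and an odds ratio of 2 at 10%/5% by about 1.7. At high rates the gap can narrow. These sizes rest wholly on assumed race-specific rates and a common odds ratio. The three main hypotheses, which compare arms, and the knowledge analysis are untouched.

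**What to change.** Keep the logistic interaction. Beside it, for discussion, intentions, referral and completion, report:

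- the rates by arm within African American and White patients; and
- the difference in risk differences, that is, the change in the White minus African American gap between Comparison and Multilevel Clinics, with a 95% confidence interval.

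Obtain both by marginal standardization from the planned logistic models that include the arm-by-race term. State that any conclusion about the equity gap in rates will rest on these estimates and not on the interaction p-value alone, and label them as exploratory estimates and not powered tests.

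The cost is a post-estimation step on models already planned, with no new data. The drawback is one more exploratory quantity, whose interval at N = 368 will probably be as wide as or wider than the gap changes of interest.
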